# 3.0 Proposed Study

This randomised, blinded, controlled trial will evaluate the efficacy and safety of dietary and behavioural counselling, exercise, Withania somnifera and a Adult Multi One multivitamin to effectively treat anxiety. This will be an intervention trial using treatments and products widely available on the market, and an indistinguishable placebo. The study sample will be randomised into two arms: treatment and control. The study population will consist of 80 Canada Post Employees.

### 3.1.2 Trial Site

The trial shall take place at the Canada Post Gateway Processing Plant, [name] under the supervision of the four investigators listed above.

### Methodology

Setting and Participants: The setting for this study will be the Gateway Processing Plant of the Canada Post Corporation in Mississauga. The study will take place from September to December, and will involve Canada Post employees and members of the Canadian Union of Postal Workers (CUPW). Workers will primarily be from the Gateway plant, however a minority of the study population will be from other Canada Post facilities. There will be a mix of workers, from day to evening to night shift letter and package sorters, to outdoor letter carriers and drivers. The study population will be male and female, in the age groups from 18 to 65.

Sampling and Recruitment: Recruitment for the study will be facilitated by Canada Post Corporation and CUPW representatives. Posters and information sheets will be posted and distributed throughout eligible sites. Interested parties will be encouraged to contact the Naturopathic Doctors directly, either by phone or e-mail and provide their name, phone number, preferred time of contact, and mailing address. Interested participants will be given an Information Kit, which will include: a sample consent form, a Backgrounder explaining the purpose of the study, a description of Naturopathic Modalities, a question and answer sheet regarding the study, contact list and phone numbers of the Naturopathic Doctors, Canada Post, and CUPW representatives involved in the study, and the Naturopathic Doctors business cards. The two trial coordinators will also conduct brief information sessions at the pre-shift meetings. Interested participants will be encouraged to ask questions to their Canada Post or CUPW representatives, and directly to the Naturopathic Doctors. Following the mailing of the Information Kit, interested participants will be contacted by telephone, screened for stress and or anxiety and availability for the entire duration of the study, and scheduled for a 1 hour initial consultation in a designated room at the Canada Post Gateway Processing Plant. At this consultation, any outstanding questions will be answered by the Naturopathic Doctors, a waiver and consent form will be signed and witnessed, and the intake interview and physical exam to evaluate the eligibility for the study will take place. At the end of the initial visit, potential participants will be instructed to complete the Beck Anxiety Inventory, S-90-R, SF-36, and a Fatigue Questionnaire. A minimal score on the Beck Anxiety Inventory, as well as absence of any contraindications found on the initial intake, will be used to determine eligibility for the study.

At the conclusion of the initial visit, participants will receive the Diet, Absenteeism, Medication and Therapies Diary (Appendix I) chart to complete at home over the next week. Eligible participants will be randomly assigned to either the control or treatment groups, and will be booked for further appointment times.

On subsequent visits, both the control and intervention group patients will receive treatments including cognitive behavioural stress reduction, behavioral psychotherapy, examination of sleep patterns and treatment for any insomnia. Both groups will be encouraged to engage in an active exercise routine. The active group will also receive daily good quality multi vitamin (Ultra Balance III by Douglas Labs) and *Withania somnifera* (300 mg standardized to 1.5% Withanolides, bid) (Ashwagandha by Douglas Labs). The control group will receive placebo identical in look and frequency of dosage to the treatment group. On subsequent visits, the active group will receive lifestyle and diet counseling, and will continue with behavioral psychotherapy. Active group patients will also receive acupressure massage for at least 15 minutes once per week.

Both the active and control arm will attend weekly 30 minute treatments, for a total of 12 treatments over 12 weeks. Both groups will complete the Beck Anxiety Inventory, S-90-R, SF-36, Fatigue Questionnaire, and the Perceived Benefit of Treatment questionnaires at 4, 8, and 12 weeks. At these times, the sitting and orthostatic blood pressures will also be recorded. Both groups will also hand in the Pain Diet, Absenteeism, Pain Medication and Therapies Diary every week.

Study period is 12 weeks. Clinical evaluations will be performed at:

- Baseline (Visit 1 - Day 1)
- Interim for the treatment groups: (Visit 2 - Day 7, Visit 3- Day 14, Visit 4 – Day 21, Visit 4 – Day 28, Visit 5 – Day 35, Visit 6 – Day 42, Visit 7 – Day 49, Visit 8 – Day 56, Visit 9 – Day 63, Visit 10 – Day 70, Visit 11 – Day 77)
- Interim for the control groups: (Visit 2 - Day 7, Visit 3- Day 14, Visit 4 – Day 21, Visit 4 – Day 28, Visit 5 – Day 35, Visit 6 – Day 42, Visit 7 – Day 49, Visit 8 – Day 56, Visit 9 – Day 63, Visit 10 – Day 70, Visit 11 – Day 77)
- End of Treatment (Visit 12 - Day 84), Questionnaires and Medication diaries filled in for the last time

Follow-up data will be collected at 2, 6, and 12 months post treatment via a mailed questionnaire package containing the Beck Anxiety Inventory, S-90-R, SF-36, Fatigue Questionnaire, and the Perceived Benefit of Treatment questionnaires, as well as the Diet, Absenteeism, Medication and Therapies Diary. Non-responders will receive reminders by post. If this is unsuccessful, the patients will be telephoned.

### 3.1.4 Design

Single blinded, randomised, controlled intervention trial..

### 3.1.5 Patient Selection

80 healthy subjects irrespective of ethnicity, aged 18 to 65 that are self-selected through response to local ads and information talks through Canada Post Centres in Toronto. Contraindications will be ruled out first and informed consent must be received from all participants before eligibility is assigned. Mild anxiety must be exhibited, and a score of 10 must be achieved on the Beck Anxiety Inventory administered on intake in order for patients to qualify.

## 3.2 Inclusion/Exclusion Criteria

### 3.2.1 Inclusion Criteria

1. Males and females aged 18-65 that are Canada Post employees and members of Canadian Union of Postal Workers (CUPW).

2. Mentally competent subjects able to adhere to the given protocol and treatments administered as interventions.

3. Self-selected candidates identifying themselves to suffer from the symptoms of stress and anxiety for a period of 6 weeks or more and a score of at least 10 on the BAI at the pre-study intake.

4. Normal on physical examination at the pre-study intake, and in the case of abnormalities the medical practitioner considers them to be clinically insignificant.

5. Written and informed consent.

6. The potential candidate must have a family doctor that they have seen in the last 12 months.

### 3.2.2 Exclusion Criteria

1. Mentally or physically incapacitated such that informed consent cannot be obtained.

2. Any history or other condition which the study physician regards as clinically significant to the study (including allergies or sensitivities to withanolides or multivitamins).

3. A major illness considered to be clinically significant by the study physician within 3 months of the study start date.

4. Current participation in another intervention trial.

5. Pregnancy or intent to become pregnant in the next 6 months.

6. Medication at doses that is contraindicated with herb/multi-vitamin. (specifically daily use of benzodiazepene class drugs.)

7. Current alcoholism or substance abuse (sedative)

8. Current history of tumors.

9. Any current serious disorders determined to be clinically significant to the study.

.

## 3.3 Timeline

1. Labelled as day 0, all potential candidates will be screened for inclusion/exclusion criteria by being asked to read and sign the informed consent, fill in questionnaires including the BAI, be clinically assessed, have their blood pressure taken, and have urine tests to assess for proper liver and kidney function.

1. On day 1, participants that have fulfilled all eligibility criteria and completed the consent form will be randomised into either treatment or control groups using a random number generator by the research assistant who will label the containers of placebo, *Withania somnifera* and multivitamin respectively.
2. Both treatment and placebo groups shall receive the visually identical capsules by the study co-ordinator with instructions on the dosage schedule.
3. Both groups shall take their medications twice daily, one capsule in the morning and one in the evening prior to meals.
4. The treatment shall last 90 days.
5. On day 1, subjects will be clinically assessed, have their blood pressure taken, be interviewed, and complete the SCL-90R, SF-36 and fatique questionnaires. Medication usage will be monitored and compliance to the interventions will be assessed.
6. On day 7, subjects will receive cognitive–behavioral therapy, dietary advice and stress reduction techniques. They will continue these treatment sessions 1 time per week until the completion of the study. (Day 14, 21, 28, 35, 42, 49, 56, 63, 70, 77 and 84)
7. On day 8, subjects in the active group will receive acupressure massage in the treatment of anxiety. They will continue these treatment sessions 1 time per week until the completion of the study. . (Day 15, 22, 30, 38, 45, 52, 60, 68, 75, 82 and 90)
8. On day 28, subjects will be clinically assessed, have their blood pressure taken, be interviewed, and complete the SCL-90R, SF-36 and fatigue questionnaires
9. On day 56, subjects will be clinically assessed, have their blood pressure taken, be interviewed, and complete the SCL-90R, SF-36 and fatigue questionnaires
10. On day 84, subjects will be clinically assessed, have their blood pressure taken, be interviewed, and complete the SCL-90R, SF-36 and fatigue questionnaires

Adherence to the schedule and adverse effects will be assessed at patient interviews at each stage of the study. In addition, subjects will have access by phone or visit to the supervising physician if they feel their health is being compromised in any way during the study. As a way of measuring and promoting compliance, subjects will be given study calendars and asked to return their unfinished pills.

.

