## 5.1 Time Line

The subjects will be directly involved in the study for twelve weeks. We intend on recruiting for the trial immediately upon approval of the trial by Health Canada. Recruitment should take three to six weeks and if possible be complete before the end of October. We will commence with treatment after recruitment of 80 eligible participants, which is projected to early November. The trial itself will be completed by the end of January 2006. Data analysis will ensue followed by publication in a peer reviewed article sometime in the Winter of 2006.

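### Allocation names only a random number generator, with no arm sizes, blocks or strata, and the named tests are unadjusted, so precision and baseline balance are given up that the timeline would allow

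*Protocol*

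**What the plan says.** - **Method.** Protocol Section 3.3 (Timeline) says that on Day 1 participants are "randomised into either treatment or control groups using a random number generator by the research assistant". Section 3.1.4 adds only "Single blinded, randomised, controlled intervention trial". No section shown gives an allocation ratio, arm sizes, blocks, strata or minimisation.
- **Timing.** Under Methodology (Sampling and Recruitment), after the initial visit, "Eligible participants will be randomly assigned to either the control or treatment groups, and will be booked for further appointment times". Section 3.3 places randomisation on Day 1, the day after screening. Section 5.1 says: "We will commence with treatment after recruitment of 80 eligible participants, which is projected to early November".
- **Information available beforehand.** At Day 0 candidates "fill in questionnaires including the BAI, be clinically assessed", and the schedule of events also puts the BAI at Day 0. The demographic form, which carries the screening date, has an occupation field. No form shown has a field for shift.
- **Population.** Methodology: "There will be a mix of workers, from day to evening to night shift letter and package sorters, to outdoor letter carriers and drivers".
- **Analysis.** The Statistical Analysis section names the chi-square test and Student's t-test, with no covariate. It names a different rating scale; the BAI is assumed here. It does not say whether the t-test is on final or change scores.
- **Size.** The sample size section requires 54 completers (80% power, two-sided 5%) and 78 starters at 30% dropout. Other sections say 80.

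**The concern.** With rolling entry, the usual argument against tight balancing is that later assignments become predictable. That argument falls away if the whole sample is in hand before anyone needs an arm, as Section 5.1 implies. An exact 40:40 split balanced on entry severity would then be available at almost no cost, and the Protocol does not call for it.

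What is at stake is how precise and readable a trial of about 54 completers will be. If the arms differ visibly at entry and the comparison is unadjusted, readers will find the result hard to interpret, and variance that baseline BAI could explain stays in the error term. The three statements on timing also matter, because whether allocation is a single batch or rolling decides which balancing scheme can be used.

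**Working it through.** **The plan's own figure.** 54/(1 − 0.30) = 77.1, rounded up to 78, which reproduces. The 54 cannot be derived independently because no SD or baseline mean is given. Back-solving for 27 per arm: d = (1.960 + 0.842) × √(2/27) = 0.762 SD by the normal approximation, or about 0.78 SD by the t distribution.

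**Arm sizes under simple allocation of 80.** From Binomial(80, 0.5), a split of 46:34 or worse has probability 21.9%. The relative efficiency at that split is 4 × 34 × 46/80² = 0.978. Power averaged over chance arm sizes with 54 completers is 79.2% against 80%. Unequal arms alone therefore cost little.

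**Baseline BAI gap above 0.3 SD, normal scores assumed.**
- Simple allocation, 54 completers: SD of the gap = √(2/27) = 0.272; 0.3/0.272 = 1.10; probability 27%.
- Stratified at the median, 40:40, then random loss to 27 per arm. The within-stratum share of variance is 1 − 2/π = 0.363. The between-stratum share, 0.637, is multiplied by (40 − 27)/39 = 1/3. Variance = (2/27) × (0.363 + 0.637/3) = 0.0426; SD = 0.206; 0.3/0.206 = 1.45; probability about 15%.

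**Power at d = 0.762, 27 per arm, assumed correlation ρ = 0.5 between baseline and outcome.** Normal approximation: Φ(d√13.5/√v − 1.96), where v is the residual variance.

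| Analysis | v | Normal approximation | Simulation with t critical values |
| --- | --- | --- | --- |
| Unadjusted t-test, simple allocation | 1 | 80% | about 79% |
| Strata in model, stratified allocation | 1 − 0.25 × 0.637 = 0.841 | 86% | 85% to 86% (d from 0.762 to 0.777) |
| Continuous baseline, simple allocation | 1 − 0.25 = 0.75 | 90% | about 88% |
| Continuous baseline, stratified allocation | 0.75 | 90% | about 88% to 89% |

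If completer numbers per arm also vary by chance, the simulated figures for simple allocation are 77% (t-test) and 87% (continuous baseline). For ρ = 0.3 and 0.7, baseline-adjusted power by the normal approximation is 84% and 97%.

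**Type I error.** The t-test under simple allocation simulates at 4.9%, which is nominal. Balancing without adjusting makes it conservative: 2.3% when pairs are matched on BAI at ρ = 0.5.

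**Job type.** The shares are not given. For a job type held by an assumed 20% to 50% of 80 people split 40:40 without stratification, the arms differ by 15 percentage points or more with probability 16% to 26% (hypergeometric).

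**The case against.** **The scheme is inferred from silence.** A random number generator is a source of randomness, not a scheme, and permuted blocks or stratified lists use one too. This stands: a reader might infer that the trial definitely uses simple randomisation, but the text shows only that no restriction is stated. Simple allocation is the comparison case here. The omission is still a protocol matter, because the research assistant must act on it before any analysis plan applies.

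**Chance imbalance is not bias.** Its variability is already in the t-test's standard error. This also stands. A reader might compute that a 0.3 SD gap at a correlation of 0.6 carries over as 0.18 SD, some 23% of a 0.78 SD effect, and treat that as added damage. The documents do not support that reading. The error rate is nominal, and the direction depends on an analysis that the Protocol does not fix: on change scores the same gap shifts the result by 0.3 × (1 − 0.6) = 0.12 SD the other way.

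**The gain from balancing is easily overstated.** For all 80 randomised, the chance of a gap above 0.3 SD is 18% with simple allocation and 2.6% with median stratification. The comparison rests on completers, where it is 27% against about 15%. With continuous baseline BAI in the model, stratifying adds only about a point of power at ρ = 0.5.

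**Job type and shift.** Nothing in the Protocol shows that either predicts BAI response, and only occupation is recorded. Stratifying on job type is therefore optional, and on shift not possible unless it is collected.

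**The single batch is uncertain.** It rests on Section 5.1. Methodology and Section 3.3 read as participant-by-participant allocation, and Methodology's September to December calendar differs from Section 5.1's November to January. The fix must therefore cover both cases.

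**Conclusion.** The point holds as a loss of precision and baseline balance, not as a threat to validity. The Protocol states no restriction on allocation and no adjustment, while its own timeline would have Day 0 BAI and occupation in hand for all 80 before treatment. The size is moderate: the chance of a completer baseline gap above 0.3 SD could roughly halve, from about 27% to about 15%, and power could rise by about 7 to 10 points, mostly through adjustment. These figures assume normal scores, dropout unrelated to BAI, 27 completers per arm, a correlation of 0.5 and the effect size implied by 54 completers. They also take the t-test to be on final scores. The change is worth making because it is cheap.

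**What to change.** 1. Reconcile Methodology (Sampling and Recruitment), Section 3.3 and Section 5.1 on when allocation happens.
2. **If it is a single batch:** after the 80th participant is confirmed eligible, draw one 40:40 allocation stratified by Day 0 BAI (above or below the median, with a stated side for ties). If wanted, add one coarse job-type factor taken from the recorded occupation; use shift only if it is recorded at intake. Settle odd-sized strata at random so that the total stays 40:40.
3. **If entry is rolling:** use randomly varying block sizes, stratified by a BAI cut-point fixed in advance, since the sample median is not yet known.
4. **In either case:** adjust the primary BAI comparison for Day 0 BAI as a continuous covariate and for any stratification factor. Stratifying without adjusting would leave the t-test conservative.

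The cost is a short script for the research assistant, a few sentences of Protocol text and one or two extra model terms. No added participants, visits or staff are needed.

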**Setting:**

The Gateway Processing Plant is an ideal institution from which to adequately supervise and conduct the study. Study participants will be volunteers recruited from Canada Post employees through advertisements in corporate newsletters, information and talks led by the trial investigators. Participants will be fully informed of the treatment they may receive and must give informed consent before enrolment.

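### The two arms are defined inconsistently: control-arm diet counselling is contradicted, active-only acupressure is missing from the hypothesis, and the blinding claim goes further than the masked capsules

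*Protocol*

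**What the plan says.** **Acupressure.** Section 3.3 Timeline, item 7, states: "On day 8, subjects in the active group will receive acupressure massage in the treatment of anxiety", with weekly sessions thereafter. The Methodology agrees: "Active group patients will also receive acupressure massage for at least 15 minutes once per week". The Outcome measurements paragraph includes acupressure in the package whose effect on the BAI is to be determined. The objective, null hypothesis and arm definitions in section 2.0 do not mention it, nor does the treatment list in section 3.0.

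**Diet counselling for control.** The Participants paragraph of section 2.0 lists dietary modification for control. The Intervention paragraph of the same abstract lists dietary counselling for the active arm and omits it for control. The Methodology says: "On subsequent visits, the active group will receive lifestyle and diet counseling, and will continue with behavioral psychotherapy". Timeline item 6 gives "dietary advice and stress reduction techniques" to subjects, with no arm named.

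**Masking.** Section 3.0 calls the trial blinded with an indistinguishable placebo; section 3.1.4 calls it single-blind. Neither says who is blinded. The Methodology states: "The control group will receive placebo identical in look and frequency of dosage to the treatment group". Timeline item 2 repeats it: "Both treatment and placebo groups shall receive the visually identical capsules". The Statistical Analysis paragraph adds that the analysis is run on coded subjects. The Setting paragraph says: "Participants will be fully informed of the treatment they may receive and must give informed consent before enrolment". Appendix A shows that participants complete the BAI themselves.

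**The concern.** Two things are at stake.

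The first is what the randomised comparison tests. A two-arm trial informs on the components that differ between arms. If the document does not settle which components differ, a significant result has no fixed meaning. A reader of the abstract would credit Withania and the multivitamin; a reader of the Methodology would also have to credit diet counselling and massage.

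The second is how far the word blinded can be trusted. Identical capsules cannot conceal a hands-on session that one arm receives and the other does not. Coded analysis does not protect a questionnaire that participants fill in themselves. A reader told that the trial is blinded would not allow for reporting bias on the BAI.

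**Working it through.** No figure stated in the protocol depends on this point, so the check is a comparison of texts with a few counts.

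**Step 1. What differs between arms, by place.**

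| Place in protocol | Diet counselling for control | Acupressure | Components in the active arm only |
|---|---|---|---|
| 2.0, Participants | given | not mentioned | Withania, multivitamin |
| 2.0, Intervention | not listed | not mentioned | Withania, multivitamin, diet |
| Methodology | stated for active only | active only | Withania, multivitamin, diet, acupressure |
| 3.3 Timeline, items 6 and 7 | given, by its wording | active only | Withania, multivitamin, acupressure |

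Four places give four different contrasts. The first two rows belong to the same abstract, so this is not merely a summary differing from a detailed section.

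**Step 2. The null hypothesis against the arms.** The null hypothesis in section 2.0 names five components: diet, exercise, counselling, Withania and multivitamin. The Participants paragraph gives the first three to control as well. That leaves 5 − 3 = 2 that differ. The comparison as randomised cannot test the five-component statement, and acupressure, which the Methodology and Timeline assign to the active arm, is not among the five.

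**Step 3. The two discrepancies differ in kind.** On diet, the passages contradict each other. On acupressure they do not: no passage gives it to control, and the Methodology and Timeline agree that it is active-only. There the fault is omission from sections 2.0 and 3.0.

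**Step 4. What is masked, and for whom.** Participants: capsule content only. Analysts: arm labels, through coding. Acupressure: no sham or matched session is described. Outcome: self-rated. Masked capsules and masked analysis together still leave the BAI open to a participant's awareness of receiving an extra treatment.

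**Step 5. Does contact time differ?** The Methodology says: "Both the active and control arm will attend weekly 30 minute treatments, for a total of 12 treatments over 12 weeks". That is 12 × 30 = 360 minutes in each arm.
- Massage on the separate days listed in the Timeline: 11 of the 12 days fall by the Day 84 assessment (the last is Day 90). With the Methodology's 15-minute minimum this adds at least 11 × 15 = 165 minutes, so at least 525 against 360.
- Massage inside the 30-minute visit, which the Methodology alone would allow: 360 against 360.

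Unequal contact therefore depends on which passage is followed. Neither reading converts into BAI points.

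**The case against.** A package compared with an active control is a legitimate pragmatic design. The Relevance paragraphs and Outcome measurements make clear that combined care is the target, so the lack of a sham massage is not in itself an error. This stands, and no sham is asked for here.

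Participant blinding is never stated outright. Single-blind could refer to the analyst, since coded analysis is the one form of blinding described explicitly. This stands in part. The indistinguishable placebo points to participants, and if only analysts were meant, the document should say so.

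A reader might infer that participants were in fact unblinded. The document does not support that. The Setting paragraph says they are told what they may receive, not which arm receives what, and the consent pages are not shown. Only a risk can be asserted.

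A reader might also infer that the active arm received more attention and that the result is biased in its favour. Contact is equal on one reading of the Methodology, and nothing in the document links contact or awareness to BAI points.

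Finally, the schedule of events in Appendix F has no acupressure row, but this is weak evidence. Its columns (Days 0, 1, 28, 56 and 84) include no acupressure day, and it has no diet or exercise row either. It is not relied on here.

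On diet, the Methodology introduces its list of treatments common to both arms with the word including, which might be read as open-ended. Even so, that would not reconcile the two paragraphs of the abstract.

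**Conclusion.** The point holds in three parts.

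- Control-arm diet counselling is contradictory: given in the Participants paragraph of section 2.0 and, by its wording, in Timeline item 6; absent from the control list in the Intervention paragraph; stated only for the active group in the Methodology.
- Acupressure is active-only and part of the tested package, but is omitted from the objective, null hypothesis and arm definitions in section 2.0 and from section 3.0. The null hypothesis names five components of which section 2.0 gives three to both arms. Which components differ depends on the passage followed.
- The blinding claim is broader than the masking described, and participant blinding on the self-rated BAI is at risk. This rests on inference, because the blinded party is not named and the consent pages are not shown.

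The size and direction of any bias cannot be derived. It would also go too far to say that an observed difference can come only from the active-only components: reporting bias and chance could contribute. The inconsistencies should be corrected because they govern what the trial can conclude. Arm definitions and the blinded party are not details that a protocol leaves to an analysis plan.

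**What to change.** 1. Use one intervention list and one schedule per arm, identical in section 2.0 (Participants and Intervention), section 3.0, the Methodology, section 3.3 and Outcome measurements. State whether control receives diet counselling.
2. Restate the objective and null hypothesis as the whole package, including acupressure, versus active control. List the active-only components, and state that a difference will not be attributed to Withania or the multivitamin alone.
3. Replace the blinding description with: *capsule content masked and statistical analysis blinded; acupressure not masked*.

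These are text changes; care and sample size are unaffected. Section 5.3 says that registration followed completion, so if the trial has run, the arm lists must match what was delivered, which means checking treatment records. Rewording cannot add masking after the fact; it can only make the description accurate. The price is a narrower and less favourable claim.
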